### Statistical analysis

Our study design includes two intervention groups and three repeated measurements (baseline, 4 weeks, final visit). To control for correlated observations per subject per visit, the analysis of outcomes will be by linear mixed model regression. This model will include the treatment covariate, the visit covariate and their interaction term and a random term to control for within-subject correlation. The primary outcome variable is change in body weight. The interaction term will indicate change over time in body weight by intervention group. Depending on the pattern of missing observations and loss to follow-up, missing values will be handled with multiple imputations or model approaches (including linear mixed models which are robust to missing observations), and sensitivity analyses will be performed as recommended [40, 41].

We expect that there will be treatment heterogeneity indicating that effects may differ depending on covariate values at baseline. For example, baseline body weight is highly predictive and correlated to body weight change during an intervention. All models will thus be adjusted for the baseline values of the outcome variable. In addition, the models will be adjusted for the blocking factor used in randomization.

The analyses will be performed according to the intention-to-treat approach, but per-protocol (in which noncompliant participants are excluded) analyses will also be reported as recommended by the CONSORT guidelines [21].

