**Method/design:**

Men and women (calculated sample size = 60), aged 18–45 years, with body mass index of 27–35 kg/m^2^ will be included in a double-blind 8-week dietary intervention study. The participants will be randomized in a 1:1 manner to a diet with either low or high SAA. Both groups will receive an equal base diet consisting of low-SAA plant-based whole foods and an amino acid supplement free of SAA. Contrasting SAA contents will be achieved using capsules with or without methionine and cysteine (SAA_high_, total diet SAA ~ 50–60 mg/kg body weight/day; SAA_low_, total diet SAA ~ 15–25 mg/kg body weight/day). The primary outcome is body weight change. Data and material collection will also include body composition (dual X-ray absorptiometry), resting energy expenditure (whole-room indirect calorimetry) and samples of blood, urine, feces and adipose tissue at baseline, at 4 weeks and at study completion. Measures will be taken to promote and monitor diet adherence. Data will be analyzed using linear mixed model regression to account for the repeated measures design and within-subject correlation.

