### Sample size

Little is known about the effects of a SAA restricted diet on body weight and we have thus based power calculations on data from generic vegan interventions [38]. The online tool GLIMMPSE (https://v2.glimmpse.samplesizeshop.org) was used for power calculations [39]. With two groups and three repeated measures we will test for a significant group by time interaction in the study, indicating differences in body weight over time between the groups. Desired power is 0.8 and alpha was set to 0.05. A body weight difference of 3 kg between groups at the end of the study is considered clinically meaningful. The average body weight at baseline was set to 90 (SD 6) kg. A mean body weight difference of 1 and 3 kg between the SAA_low_ and SAA_high_ after 4 weeks and 8 weeks was set in the power calculations, respectively. Baseline body weight is generally strongly correlated with body weight at subsequent visits. We hypothesize a correlation of 0.9 between repeated measurements of body weight in each subject at each study visit and a decay rate of this correlation coefficient of 0.5 per visit. This yielded a total sample size of 46. Accounting for 25% dropout (46/1 − 0.25), the total sample size is 60 corresponding to 30 participants per group. The design file used for sample size calculations is available in the supplementary material and can be uploaded to GLIMMPSE to view results and design choices (Additional file 3).

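### With a lone random term, the week-8 weight difference gets a standard error about 11% too small under the protocol's own decaying correlation, while the powered interaction test is barely affected

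*Protocol article*

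**What the plan says.** The Statistical analysis section of the protocol article lists the contents of the mixed model: treatment, visit, their interaction, and "a random term to control for within-subject correlation". It states no residual covariance. It names change in weight as the primary outcome and adjusts every model for the baseline value.

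The Sample size section describes the within-subject correlation differently. It says "We hypothesize a correlation of 0.9 between repeated measurements of body weight in each subject at each study visit", together with "a decay rate of this correlation coefficient of 0.5 per visit". The test that was powered is also given there: "With two groups and three repeated measures we will test for a significant group by time interaction in the study". The error rate is attached to that test: "Desired power is 0.8 and alpha was set to 0.05". The same section takes a 3 kg gap between the groups at the end of the study as the difference that matters clinically.

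**The concern.** A single random term whose stated job is to handle within-subject correlation is ordinarily a subject random intercept with independent residuals. That model forces one correlation on all pairs of visits, and hence one variance on the week-4 and week-8 changes. If correlation decays with time, as the sample size assumes, the week-8 change is more variable than the week-4 change. The model averages the two, so the week-8 standard error comes out too small and the week-4 one too large.

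The week-8 difference is the estimate in kilograms that readers will set against 3 kg; a joint interaction test gives no such estimate. An interval that is too narrow there affects the trial's main numerical result.

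**Working it through.** **Inputs.** From the Sample size section: "The average body weight at baseline was set to 90 (SD 6) kg", and "A mean body weight difference of 1 and 3 kg between the SAA_low_ and SAA_high_ after 4 weeks and 8 weeks was set". The base correlation is 0.9 with decay 0.5 per visit, power 0.80 and alpha 0.05. Allocation is 1:1 (Abstract, Method/design). Assumptions: SD 6 kg at all three visits, no group difference at baseline, and complete data unless stated.

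**Step 1: reproduce 46.** Read the decay as a linear-exponent autoregressive structure: 0.9 for adjacent visits and 0.9^1.5 = 0.8538 for baseline to week 8. The changes from baseline to weeks 4 and 8 then have:
- variances 72 × (1 − 0.9) = 7.20 and 72 × (1 − 0.8538) = 10.525
- covariance 36 × (0.9 − 0.9 − 0.8538 + 1) = 5.263

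With differences d = (1, 3), d′S⁻¹d = (10.525 − 2 × 3 × 5.263 + 9 × 7.20) / (7.20 × 10.525 − 5.263²) = 43.75 / 48.09 = 0.910. At 23 per group the noncentrality is (23/2) × 0.910 = 10.46. The Hotelling-Lawley F test on 2 and 43 degrees of freedom has power 0.805; N = 44 gives 0.785. So 46 is reproduced. Other readings do not fit:
- equal correlation of 0.9 gives 34
- decay to 0.81 (first-order autoregressive) gives 58
- literal halving to 0.45 is not a valid correlation matrix

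**Step 2: week-8 difference, three-visit random intercept.** The mean correlation is (0.9 + 0.9 + 0.8538)/3 = 0.8846, so the modelled residual variance is 36 × (1 − 0.8846) = 4.154 and the modelled variance of any change is 8.308.
- Model SE = √(8.308 × 4/46) = 0.850 kg.
- True SE = √(10.525 × 4/46) = 0.957 kg.
- Ratio = 0.888, about 11% too small.
- Error rate = 2 × P(Z > 1.96 × 0.888) = 8.2%. Simulation gives 8.1% to 8.3%.

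A nominal 95% interval has half-width 1.96 × 0.850 = 1.67 kg where 1.96 × 0.957 = 1.88 kg is needed, and covers about 92%.

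**Step 3: week-4 difference.** True SE = √(7.20 × 4/46) = 0.791 kg; ratio 0.850/0.791 = 1.074; error rate about 3.5%. This contrast is conservative.

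**Step 4: joint 2-df interaction test.** The modelled covariance of the two changes is 4.154 × [2, 1; 1, 2]. Relative to it, the true covariance has eigenvalues 0.733 and 1.267, which sum to 2. The Wald statistic is the corresponding weighted sum of chi-squares and exceeds the 5% critical value with probability 5.3% (simulated 5.2% to 5.5%).

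**Step 5: change as outcome, baseline as covariate.** Only weeks 4 and 8 remain as responses. Given baseline, the variances are 36 × (1 − 0.9²) = 6.84 and 36 × (1 − 0.8538²) = 9.756. One common baseline slope adds 36 × 0.0231² = 0.019 to each, where 0.0231 = (0.9 − 0.8538)/2. The model uses the mean, 8.317, against 9.775 for week 8. The ratio is √(8.317/9.775) = 0.922, and the error rate is 7.1% (simulated 7.0% to 7.4%). With a single pair of visits, equal correlation is no restriction; the cause here is unequal variance. The 1-df group-by-visit interaction in this version stays at 4.9%.

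**Step 6: dropout and remedy.** With 60 randomised and 25% random dropout, refitted three-visit models gave 7.7% to 8.9% for week 8, depending on when dropout occurs, and the change version gave 6.5% to 7.2%. With an unstructured covariance on complete data the week-8 test is at 5.0% to 5.1%.

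**The case against.** The strongest reply is that the article never says random intercept and never says that residuals are independent. A random subject term can sit beside a structured residual covariance, and an article commonly leaves that detail to the analysis plan. This stands as a limit: the finding is conditional on the ordinary reading of the sentence. It does not dispose of the point, because the section does state a device for the correlation, and on that reading the device cannot represent the correlation behind the sample size.

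Two stronger readings are tempting and are not supported. A reader might infer that the trial's stated 5% error rate is breached. The protocol attaches alpha to the group-by-time interaction, which stays at about 5.3%, and it nowhere names a week-8 contrast as the primary test. A reader might also infer a rate of about 10%. That needs a baseline-to-week-8 correlation of 0.81 (10.5%), which would call for 58 participants rather than the stated 46. Random dropout did not bring the rate to 10% either.

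It can also be said that an unstructured covariance is a matter of taste. Here it is the choice that agrees with the planning assumptions and brings the week-8 test back to its nominal level.

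**Conclusion.** The point holds in a limited form. If the single term is a random intercept with independent residuals, the week-8 group difference would be reported with a standard error about 11% too small in the three-visit model. A nominal 5% test of it would run at about 8%, or about 7% in the baseline-adjusted change version. The main inference on the joint interaction is sound.

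This rests on an SD of 6 kg at every visit and on the linear-exponent reading of the decay, which exact reproduction of 46 supports. It rests also on the random-intercept reading, which the text suggests but does not fix. The change is recommended rather than essential, with moderate confidence.

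**What to change.** For the primary outcome, replace the lone random term by an unstructured within-subject covariance over the visits, fitted by REML with Kenward-Roger degrees of freedom. Name one fallback in advance in case it does not converge: for example, heterogeneous Toeplitz in the three-visit form. With only two post-baseline visits that coincides with unstructured, so robust standard errors would serve there. State that the week-8 group difference and its 95% interval will be reported from this model. If a structured residual covariance is already intended, saying so settles the matter.

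The cost is a sentence or two in the analysis section. The covariance has six parameters instead of two over three visits, or three instead of two over two visits. That is estimable with 46 to 60 participants, at slightly fewer degrees of freedom. Planned power is not given up: the test that reproduces 46 at power 0.805 already leaves the covariance unrestricted.

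### Baseline weight is both a response visit and a covariate in the primary mixed model, so the planned baseline adjustment brings essentially no precision to the treatment-by-visit test

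*Protocol article*

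**What the plan says.** All of this is in the protocol article.

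- **Responses.** Statistical analysis: "Our study design includes two intervention groups and three repeated measurements (baseline, 4 weeks, final visit".
- **Model.** "This model will include the treatment covariate, the visit covariate and their interaction term and a random term to control for within-subject correlation".
- **Term that carries the effect.** "The interaction term will indicate change over time in body weight by intervention group".
- **Outcome.** "The primary outcome variable is change in body weight".
- **Adjustment.** "All models will thus be adjusted for the baseline values of the outcome variable". The reason given is that baseline weight strongly predicts weight change. The models are also to be adjusted for the factor used in randomization, which the randomization section gives as sex.
- **Test used for the sample size.** Sample size: "With two groups and three repeated measures we will test for a significant group by time interaction in the study", and "Desired power is 0.8 and alpha was set to 0.05". No baseline covariate is mentioned there. A 3 kg difference at the end of the study is called clinically meaningful.

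**The concern.** The same measurement stands on both sides of the model. The baseline row of the response is regressed on itself, and a covariate that is constant within a participant cancels from any within-participant comparison. The interaction is such a comparison. The adjustment is justified by its prediction of weight change, yet as a main effect it cannot sharpen the term that measures weight change.

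Two things are at stake. The precision that a proper baseline adjustment would give is not obtained. Also, naming change as the outcome while adjusting for baseline leaves it open for an analyst to drop the baseline row. The same interaction term would then answer a different question.

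**Working it through.** **Inputs (Sample size section).** SD 6 kg; differences between arms of 1 kg at week 4 and 3 kg at week 8, and 0 at baseline by randomization; correlation 0.9 with decay 0.5 per visit; 46 participants before dropout, so 23 per arm; 25% dropout; 60 in total, so 30 per arm. Assumptions: the decay means 0.9 for adjacent visits and 0.9^1.5 = 0.854 from baseline to week 8, and alpha 0.05 is two-sided for single contrasts.

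**1. The plan's own figure.** For the changes from baseline at weeks 4 and 8:
- variances 36 × 2 × (1 − 0.9) = 7.20 and 36 × 2 × (1 − 0.854) = 10.53; covariance 36 × (1 − 0.854) = 5.26
- with d = (1, 3), d′V⁻¹d = (10.53 − 6 × 5.26 + 9 × 7.20) / (7.20 × 10.53 − 5.26²) = 43.75 / 48.09 = 0.910
- noncentrality (23/2) × 0.910 = 10.46 on F(2, 43)

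Power is 0.805 at 46 and 0.785 at 44, so 46 is reproduced by the three-visit interaction (Hotelling-Lawley).

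**2. Three response visits plus baseline as a main effect, complete data.** Random-intercept REML fits to 150 simulated data sets with 23 per arm gave the same week-8 interaction with and without the baseline covariate (largest difference below 10⁻¹² kg, mean standard-error ratio 1.0000). This is what the algebra predicts.

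**3. The same model with 25% dropout.** 30 per arm, dropout at random, half before week 4 and half before week 8:
- estimate moved by 0.08 kg on average, at most 0.26 kg
- model standard error fell from 0.839 to 0.796 (ratio 0.949)
- actual sampling SD did not fall: 1.008 without and 1.016 with the covariate

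A repeat simulation gave 0.825 to 0.783 for the standard error and 0.96 against 0.97 for the sampling SD. Part of the gap between standard error and sampling SD exists without the covariate, because a random intercept assumes constant correlation while the planning correlations decay. Only the further 5% belongs to this point.

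**4. What a working adjustment would give at week 8.**
- Unadjusted change: SD 6 × √(2 × (1 − 0.854)) = 3.24 kg; standard error 3.24 × √(2/23) = 0.957; power 0.87 for 3 kg
- Baseline as covariate only: SD 6 × √(1 − 0.854²) = 3.12 kg; standard error 0.921; power 0.89
- Variance ratio (1 + 0.854)/2 = 0.927, about 7% less

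At 30 per arm the powers are 0.94 and 0.955. The decay wording allows other readings, so the range at 23 per arm is:

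| Baseline to week-8 correlation | Unadjusted | Adjusted | Variance ratio |
|---|---|---|---|
| 0.81 | 0.77 | 0.81 | 0.905 |
| 0.854 | 0.87 | 0.89 | 0.927 |
| 0.90 | 0.96 | 0.97 | 0.950 |

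**5. Weeks 4 and 8 as the only responses.** Treatment by visit then estimates 3 − 1 = 2 kg. SD 6 × √(2 × (1 − 0.9)) = 2.68 kg; standard error 2.68 × √(2/23) = 0.791; power 0.70 at 23 per arm and 0.81 at 30. About 58 completers would be needed for 80% power (normal approximation), against the planned 46.

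**The case against.** The strongest reply is that the primary test is sound. Both the Sample size and the Statistical analysis sections speak of three repeated measures, and 46 follows from that test. Calling the outcome change does not contradict it, since using change as the response at all three visits gives the same interaction terms. The sample size never counted on a baseline covariate, so no promised power is lost. All of this stands.

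It can also be said that the text only speaks of adjustment, without fixing main effects or a covariance structure, and that an article may leave such detail to a fuller document. That stands as a limit on the exact result in steps 2 and 3. It does not remove the point, because the article itself places baseline on both sides. Adding a baseline-by-visit term alone would not cure this: the baseline row would then be fitted perfectly, and its zero residuals would enter the variance estimate.

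A reader might infer that the adjustment has no effect whatever. That is exact only for complete data and the assumed model form; with dropout the term moves slightly.

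A reader might also infer that the plan tests the wrong question, and that an effect reached by week 4 and then held would be missed almost always. The calculation gives power 0.24 if the effects are 2 then 3 kg, and 0.05 if they are 3 kg at both visits. Those figures need the two-visit reading, which goes against both statements of three repeated measures, and effect patterns that the plan does not assume.

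**Conclusion.** The point holds at moderate severity. As written, the model does not deliver the baseline adjustment that it gives a reason for, and under the planned dropout it reports a standard error about 5% smaller without real precision behind it. The primary test is not shown to be biased or underpowered: the three-visit interaction is a valid comparison of change and has the planned power. The efficiency forgone is about 7% in variance at the planning inputs (5% to 9.5% over the correlations shown), or about two percentage points of week-8 power at 23 per arm.

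The two-visit reading is a secondary risk. It is less well supported, but the wording does not exclude it, and it would move the test from the 3 kg week-8 effect to a 2 kg contrast.

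The result rests on covariates entered as main effects, a random intercept, the plan's SD and correlations, and dropout at random.

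**What to change.** Use baseline on one side of the model only, and say which:

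- **Either** model weeks 4 and 8 with treatment, visit, treatment by visit, baseline weight, baseline by visit, and sex;
- **or** keep all three visits as responses, constrain the baseline means to be equal across arms, and drop the baseline covariate.

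In both cases, name the adjusted week-8 treatment difference as the primary contrast, in place of an unspecified interaction term. Use the same form for the other outcomes measured at all three visits.

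This changes wording only, and should be settled before unblinding. It needs no new data, visits or participants: the week-8 contrast with baseline as a covariate has power 0.89 at 23 per arm, and 0.81 at the lowest correlation considered, so the planned number remains sufficient.

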### Stopping rules

Routines are implemented to identify adverse effects of the dietary interventions. Firstly, routine laboratory measures of appropriate blood biomarkers will be obtained (e.g., ASAT, ALAT, ɤ-GT, LD, creatinine) or hematological parameters including markers of B12 deficiency. Secondly, subjective measures of participant well-being are evaluated by direct questionnaires that contain questions about potential side effects, including non-specific symptoms. Individual stopping rules include allergic reactions to foods or supplement drinks, marked cardiovascular effects, fatigue or headache, or biochemical signs indicating impaired organ functions of liver, heart, kidney or blood and bone marrow.

### Strategies for data management

Data management will be handled in collaboration with the local data management team serving the Medical Faculty at the University of Oslo and handled according to the Findability–Accessibility–Interoperability and Reuse of digital assets (FAIR) principles. A data management plan has been approved by the funding organization. Data will be shared upon request and application, but will require approval from the Regional Committee for Research Ethics South-East and the Norwegian Centre for Research Data in order to comply with current privacy laws.

## Discussion

In this RCT, we will implement a dietary intervention, based on findings in animal models, to study the effects of SAA restriction on body weight, body composition and energy expenditure in humans. The diet design is similar to our previous pilot studies [19, 42] where we showed that plasma concentrations of methionine, cystathionine and urinary total cysteine decrease in SAA restricted groups along with increased serum FGF21 concentration and higher lipogenic gene expression in adipose tissue.

Presently, only one study that we are aware of has investigated the effects of methionine restriction on body composition and energy expenditure in humans [18]. This 16-weeks study with methionine restriction (but not cysteine restriction) demonstrated effects on fat oxidation, but no effects on body composition or total energy expenditure. Methionine content of the diet was controlled by using a supplement, but due to poor palatability of the supplement, 25% of the participants withdrew from the study, and poor adherence may have been a reason for the null results observed. In our pilot studies of 7 days, adherence was high, but the participants also reported poor palatability of the amino acid supplement. Thus, the restrictive nature of the diet, and poor palatability of the powder supplement make adherence a challenge in the implementation of the planned intervention. Hence, in our trial, we will take several measures to avoid drop-out. First, the strategy of the base diet has been in development over several years by personnel with nutrition background and a chef, with the aim to design a diet mainly consisting of whole foods, palatable meals, and with limited supplement intake. Second, the foods of the base diet will be delivered weekly to participant homes by a home delivery service to ensure that participants get appropriate amounts and to increase their incentive to comply. Meal plans and recipes will be sent electronically. Third, participants will be followed up on a regular basis by telephone and e-mail by study dietitians or dietitian students in their final year of training for consultation about the dietary intervention. Fourth, we will make room for an ad libitum meal per week to maintain motivation and allow social interactions with shared meals. The participants will be instructed to avoid the ad libitum meal less than three days before a study visit, as methionine metabolism after an oral methionine load may be disrupted in overweight participants [43].

